## Abstract

**Background:**

Immune checkpoint inhibitors (ICI) have revolutionised treating advanced cancers. ICI are administered intravenously every 2–6 weeks for up to 2 years, until cancer progression/unacceptable toxicity. Physiological efficacy is observed at lower doses than those used as standard of care (SOC). Pharmacodynamic studies indicate sustained target occupancy, despite a pharmacological half-life of 2–3 weeks. Reducing frequency of administration may be possible without compromising outcomes. The REFINE trial aims to limit individual patient exposure to ICI whilst maintaining efficacy, with potential benefits in quality of life and reduced drug treatment/attendance costs.

**Methods/Design:**

REFINE is a randomised phase II, multi-arm, multi-stage (MAMS) adaptive basket trial investigating extended interval administration of ICIs. Eligible patients are those responding to conventionally dosed ICI at 12 weeks. In stage I, patients (n = 160 per tumour-specific cohort) will be randomly allocated (1:1) to receive maintenance ICI at SOC vs extended dose interval. REFINE is currently recruiting UK patients with locally advanced or metastatic renal cell carcinoma (RCC) who have tolerated and responded to initial nivolumab/ipilimumab, randomised to receive maintenance nivolumab SOC (480 mg 4 weekly) vs extended interval (480 mg 8 weekly). Additional tumour cohorts are planned. Subject to satisfactory outcomes (progression-free survival) stage II will investigate up to 5 different treatment intervals. Secondary outcome measures include overall survival, quality-of-life, treatment-related toxicity, mean incremental pathway costs and quality-adjusted life-years per patient. REFINE is funded by the Jon Moulton Charity Trust and Medical Research Council, sponsored by University College London (UCL), and coordinated by the MRC CTU at UCL.

Trial Registration

ISRCTN79455488.

NCT04913025

EUDRACT #: 2021-002060-47.

CTA 31330/0008/001-0001;

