### Treatment schedule and assessments

2.9

Participants in Arm A will receive SOC interval ICI (480 mg nivo-lumab 4 weekly after ipilimumab and nivolumab regimens) commencing 6 weeks after their last infusion prior to randomisation.

Participants in Arm B will receive extended interval ICI, which in stage I is doubling the dosing interval of Arm A (SOC interval):

Additional tumour cohorts will mirror the renal cohort if treated with ipilimumab/nivolumab combinations (e.g. patients with melanoma) randomised at the point they proceed to nivolumab monotherapy. If treated with pembrolizumab (e.g. melanoma or mismatch repair-deficient Colorectal Cancer) with a SOC of 400 mg pem-brolizumab 6 weekly, the experimental arm for stage I will be 12 weekly administration.

Treatment will be given as part of the trial until disease progression, toxicity that precludes further treatment, participant preference or for 1 year 9 months from the start of randomised treatment (i.e. 2 years total treatment). Participants who are still responding to ICI treatment at 2 years will have the option to continue treatment off trial if part of their normal care. Participants experiencing progression on the extended dosing interval (Arm B) will be offered treatment intensification (i.e. reverting to SOC ICI dosing frequency, as per Arm A) at the participants and clinician's discretion.

The trial assessment schedule for each cohort is aligned with standard practice. Participants will be clinically assessed at baseline and every 4 weeks for the trial duration regardless of treatment status or progression. Since the COVID-19 pandemic clinical assessments are often conducted remotely, and the REFINE assessment schedule supports this, if possible, to collect all necessary clinical information and this is deemed appropriate by the investigator.

Participants in both arms have a CT with contrast of the chest, abdomen and pelvis (or Positron Emission Tomography (PET)-CT +/− brain surveillance if appropriate in the melanoma cohort) carried out at baseline and then every 12 weeks until disease progression or treatment discontinuation, whichever occurs later.

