### Tumour assessment

2.13

PFS outcome will be investigator-reported and will be based on radiological progression according to RECIST 1.1 criteria. Radiology reports will be collected and reports on progression will be reviewed blinded to treatment allocation.

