### Safety/toxicity management

2.14

ICI stimulate a host immune response against tumour cells. They can also lead to activation of self-reactive T cells that can damage healthy tissue and result in immune related adverse events (ir-AEs) which can affect any body system. A current list of ir-AEs is available to investigators in the Reference Safety Information (RSI). ir-AEs should be managed as per local and national/international guidelines.

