## Conclusion

3

REFINE is a randomised, phase II, MAMS adaptive basket trial investigating extended interval administration of ICI across multiple cancer types. Eligible patients are those responding (radiologically) to ICI at 12 weeks. The REFINE RCC cohort opened to recruitment on the 25th May 2022 and the first patient was randomised on 22nd August 2022. Subsequent cohorts will be added in the next 12 months. Stage I will recruit 160 patients to each cohort who will be randomised to SOC versus extended dose interval. Disease control will be analysed 6 months from completion of stage I recruitment, and this will inform stage II which will investigate up to 5 different treatment intervals. The REFINE Translational sub-study will investigate the pharmacokinetic and pharmacodynamic aspects of extended interval ICI treatment and health economic evaluation will evaluate the cost effectiveness of extended interval ICI.

Completion of the first 2 stages of REFINE will inform the design of a phase III trial testing extended dosing interval of administration of different ICI in responding patients across multiple indications. REFINE is being run in parallel with REFINE-LUNG, a phase III trial evaluating extending the interval of pembrolizumab in advanced non-small-cell-lung-cancer(NSCLC) [25] which is funded by the National Institute of Health and Care Research (NIHR) and co-ordinated by Imperial College.

Extending the interval of ICIs has potential benefits in improving patients' quality of life, via both reduced side effects and fewer hospital visits, and in more efficient use of healthcare services via lower drug treatment and attendance costs. REFINE and REFINE-Lung have joined a growing initiative of studies aiming to optimise treatment with ICI and these studies should be supported [26]. Reducing costs and the burden associated with treatment may improve access to ICI, allowing the global population to benefit from their transformative cancer outcomes.

An up-to-date version of the REFINE protocol can be found at: http://refine.mrcctu.ucl.ac.uk/.

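### The only named toxicity outcome depends on judged relatedness, while time since last dose differs between arms by design and sites know the allocation

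*Protocol article*

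**What the plan says.** The abstract states: "Secondary outcome measures include overall survival, quality-of-life, treatment-related toxicity, mean incremental pathway costs and quality-adjusted life-years per patient". The outcome list in Section 2.2 names the same single toxicity item, "treatment-related toxicity". Neither place lists an all-cause adverse event outcome.

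The randomised factor is the infusion interval. The renal cohort is "randomised to receive maintenance nivolumab SOC (480 mg 4 weekly) vs extended interval (480 mg 8 weekly"), and Section 2.9 gives 6-weekly against 12-weekly for pembrolizumab cohorts. Arm A starts trial treatment 6 weeks after the last infusion before randomisation.

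No masking of treatment is described. On progression, Arm B participants "will be offered treatment intensification (i.e. reverting to SOC ICI dosing frequency, as per Arm A"), an option that can be offered only if the site knows the arm. The only blinded step for outcome data is in Section 2.13: "Radiology reports will be collected and reports on progression will be reviewed blinded to treatment allocation".

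Less toxicity is an expected benefit. The Introduction lists it, and the Conclusion says: "Extending the interval of ICIs has potential benefits in improving patients' quality of life, via both reduced side effects and fewer hospital visits". Section 2.18 brings safety information into the choice of stage II arms when the PFS result is inconclusive.

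**The concern.** A causality filter is harmless when the judgement behind it is made in the same way in both arms. Here one natural cue for that judgement, how long ago the last dose was given, is set by randomisation. An assessor with no preference between the arms, applying one timing rule consistently, would still attribute fewer Arm B events. An assessor who keeps in mind that Arm B patients receive less drug could lean the same way.

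The Introduction shows why timing is an unreliable cue. It gives a half-life of 2–3 weeks, which invites doubt about an event seven weeks after a dose. In the same sentence it reports receptor occupancy above 70% for at least 2 months, under which that event could well be drug-related.

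At stake is whether an observed toxicity difference can be read as a true one. Fewer infusions may truly reduce toxicity, but a comparison filtered on attribution cannot separate that from a difference in attribution, and the possible bias runs towards the hoped-for result.

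**Working it through.** The article gives no figure for toxicity, so there is no stated number to reproduce. The check has two parts: what the design fixes, and what follows under assumptions.

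**Fixed by the design: share of on-schedule time beyond the standard interval after a dose**

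- Arm B, nivolumab: (8 − 4)/8 = 50%.
- Arm B, pembrolizumab: (12 − 6)/12 = 50%.
- Arm A: 0% once maintenance is under way. Before the first trial dose, a patient randomised early can spend up to 6 − 4 = 2 weeks beyond it (Sections 2.5 and 2.9).
- Scheduled ascertainment does not differ: clinical assessments are 4-weekly in both arms (Section 2.9).

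**Illustration under assumptions**

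From the document: 80 patients per arm (Section 2.3). Assumed: true event risk t equal in both arms; at most one counted event per patient, spread evenly over time; probability a that an event within the standard interval is called related; probability r × a for a later event.

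- Arm A: pA = t·a
- Arm B: pB = t·a·(1 + r)/2
- Ratio: pB/pA = (1 + r)/2, whatever t and a are
- Chance of a significant result favouring Arm B at two-sided 5% (matching the 95% intervals of Section 2.18): Φ[(pA − pB − 1.96·s0)/s], where s0 is the pooled and s the unpooled standard error

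Worked case, t = 0.6, a = 0.9, r = 0.7:

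- pA = 0.540; pB = 0.540 × 0.85 = 0.459; difference 0.081
- s0 = √(2 × 0.4995 × 0.5005/80) = 0.0791
- s = √[(0.540 × 0.460 + 0.459 × 0.541)/80] = 0.0788
- (0.081 − 0.155)/0.0788 = −0.94, so the chance is about 17%

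| r | Arm A | Arm B | Ratio | Chance (t = 0.6, a = 0.9) | Range (t 0.4–0.8, a 0.7–0.9) |
|---|---|---|---|---|---|
| 1.0 | 54.0% | 54.0% | 1.00 | 2.5% | 2.5% |
| 0.9 | 54.0% | 51.3% | 0.95 | 5% | 4–7% |
| 0.7 | 54.0% | 45.9% | 0.85 | 17% | 9–30% |
| 0.5 | 54.0% | 40.5% | 0.75 | 40% | 18–66% |

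**Off-schedule time.** If Arm B has a share f of its time beyond the standard interval and Arm A none, the ratio is 1 − f(1 − r). Halving f from 50% to 25%, an assumed value, gives 0.975, 0.925 and 0.875 for r = 0.9, 0.7 and 0.5. Late time in Arm A as well would bring the ratio still closer to 1.

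**The case against.** The strongest reply is that the outcome is a short list item in a condensed article. The article does not say who judges relatedness, by what rule, or whether all-cause events are also tabulated, and the full protocol may settle all three. That stands. A reader might infer that unblinded investigators make the judgement, or that only related events are recorded; the article states neither. What remains is that the one toxicity outcome it names is the filtered one.

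Second, the size is assumed. That attribution falls with time since dose is itself an assumption. Assessors may go by event type, using the immune-related event list in the Reference Safety Information (Section 2.14), or may know that occupancy persists and attribute late events to the drug. This stands: the illustration shows direction and plausible scale, and is not an estimate.

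Third, the 50% contrast holds only for on-schedule treatment. Discontinuation, dosing delays and Arm B reversion to the standard interval narrow it. This stands and weakens the effect without removing it.

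Fourth, a reader might infer that stage II decisions rest on this outcome. Section 2.18 speaks of safety data in general, alongside quality of life and external evidence and without strict rules. Under Section 2.22 the independent data monitoring committee sees accumulating unblinded safety data. Nothing shows that the committees see only attributed events.

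Fifth, all-cause counts are not neutral either. If Arm B progresses more often, disease-related and later-therapy events would rise there. A ratio of 1.00 for all-cause events holds only under equal true risk. This is a real trade-off, and it shapes the fix.

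**Conclusion.** The concern holds as a weakness in a stated outcome definition. The only named toxicity outcome is filtered on relatedness, sites know the allocation, and time since dose differs by arm by design. If relatedness is judged at site, and attribution falls with time since dose or with knowledge of reduced exposure, Arm B can look less toxic with no true difference.

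The size cannot be derived from the document. Under the assumptions shown, the ratio runs from 0.95 to 0.75 on schedule and is closer to 1 when off-schedule time is counted. The stronger reading, that the planned comparison is biased by a known amount, is not supported.

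The outcome is secondary, the definition of PFS is untouched, and quality of life and resource use are measured without causality attribution. This is an inexpensive improvement to make before the toxicity comparison is interpreted, and it does not put the trial's main conclusion in doubt.

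**What to change.** Define the between-arm toxicity comparison so that it does not rest on attribution alone:

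- Compare, from randomisation and whatever the attributed causality, (a) events on the immune-related list in the Reference Safety Information and (b) all-cause grade 3 or higher adverse events.
- Report treatment-related toxicity alongside, and state who judges relatedness.
- Show the same comparisons restricted to the period before progression or new anticancer therapy, because all-cause counts include disease-related and later-therapy events that may differ between arms if progression differs.

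The cost is wording in the protocol and the analysis plan. The event list and the 4-weekly assessments already exist. The eCRF needs an addition only if events judged unrelated are not already recorded. The remaining downside is some extra noise from disease-related events, which the restricted comparison reduces.

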## Introduction

1

Immune checkpoint inhibitors (ICI) have revolutionised cancer treatment over the last decade, resulting in durable responses and long-term survival in several cancer types [1–3]. ICI are monoclonal antibodies that target immune checkpoints including programmed cell death 1 receptor (PD-1) and its ligand 1 (PD-L1), which play a key role in maintaining immune homeostasis. Inhibition of these checkpoints restores the ability of the immune system to recognise and destroy cancer cells.

Despite their success, ICI impose a significant burden on patients and healthcare systems. ICI are routinely administered on a continuous schedule of frequent intravenous administrations (currently every 2–6 weeks) until cancer progression or the development of unacceptable toxicity. This approach requires a major commitment of resources for individual patients and health services alike. Disappointingly, due to the financial burden associated with treatment, ICI are not available globally to many who might benefit [4].

At present, there is limited understanding around predictive biomarkers for initial use or continued treatment with ICI, resulting in significant over treatment [5,6]. This increases treatment toxicity, negatively impacts quality of life (QOL) and has a significant and potentially avoidable financial impact on healthcare services.

Physiological efficacy of ICI (measured by PD-1 T cell receptor occupancy) is observed at much lower doses than those that have become standard of care (SOC) [7] and pharmacodynamic studies indicate sustained target occupancy on T cells of >70% for at least 2 months despite a pharmacological half-life of 2–3 weeks [8]. Furthermore, it has been observed that the rate of clearance of ICI decreases in patients responding to treatment as their disease status improves [9]. The potential prolonged physiological activity of these drugs means that as an alternative to early cessation, extending the interval of administration (i. e. reducing the frequency) should be possible, without compromising outcomes. This is supported by simulation analyses for pembrolizumab and nivolumab [10].

A number of clinical trials are currently testing early cessation in patients experiencing clinical response, either at a pre-determined timepoint such as 1 year (DANTE in melanoma or SAVE in non-small cell lung cancer [11,12]) or at maximal clinical response (SAFE-STOP and PET-STOP, in melanoma [13,14]).

REFINE (REduced Frequency ImmuNE checkpoint inhibition in cancers) is a clinical trial using a multistage approach to test whether it is possible to extend the interval between treatments in patients with metastatic cancer that are responding to ICI treatment without significantly losing efficacy [15]. There is a strong biologic rationale, coupled with potential major benefits including reduced treatment toxicity, improved QOL and reduced healthcare resource use and costs. REFINE includes a health economic component to evaluate the cost-effectiveness of extended interval treatment with ICI. Reducing costs and the burden associated with treatment may markedly improve access to ICI globally allowing populations to benefit from their transformative cancer outcomes.

## Methods

2

### Overview of design

2.1

REFINE is a phase II, multi-arm multi-stage (MAMS) basket trial investigating extended interval administration of ICI across multiple cancer types. It is a preliminary step towards a DURATIONS trial [16,17] using a MAMS approach to ultimately define a dosing interval-response curve and identify the optimal treatment schedule for ICI in patients with advanced cancer. Eligible patients should have an initial (radiological) response to ICI at 12 weeks. In stage I, patients (*n* = 160 per tumour-specific cohort) will be randomly allocated (1:1) to receive ongoing ICI as per SOC versus at extended dosing interval. The initial cohort (currently recruiting) is patients with locally advanced (inoperable) or metastatic renal cell carcinoma (RCC) who have received SOC treatment with nivolumab and ipilimumab. Responding patients (complete or partial response or stable disease on their 12-week CT scan) are randomly allocated to receive maintenance nivolumab as SOC (480 mg 4 weekly) versus extended interval dosing (480 mg 8 weekly). The next cohort to open will be melanoma and it is intended that subsequent cohorts (such as MSI high colorectal cancer) will be added in the next 12 months (Fig. 1).

Interim results will be analysed approximately 6 months from completion of stage I recruitment when the majority of patients will have had a least 9 months on trial (i.e. 1 year after starting ICI). These results will inform stage II which will investigate up to 5 different treatment intervals in subsequently recruited patients. An amendment will be submitted to the MHRA for approval prior to the commencement of the second stage.

Completion of the first two stages of REFINE will demonstrate the feasibility of recruiting to a phase III trial testing extended dosing interval of administration of different ICI in responding patients across multiple indications.

### Outcome measures

2.2

The primary outcome measure in REFINE is progression free survival (PFS). PFS is defined as the interval from randomisation to first evidence of local recurrence, new primary cancer, distant metastases (new or progression), or death from any cause, whichever occurs first. Analysis will be performed approximately 6 months after stage I recruitment has completed and will inform the design of the second stage.

The following secondary outcome measures will be analysed:

Overall survival (OS)Quality of Life (QoL) (EORTC QLQ-C30 and EQ-5D-5L)Treatment-related toxicityMean incremental cost per patientMean incremental QALYs per patient (calculated from EQ-5D-5L)Cost-utility analysis assessing cost-effectiveness of reduced versus standard frequency administrationFeasibility of recruitment to each cohort

### Sample size

2.3

REFINE will enrol 160 patients into stage I for each cohort (80 patients randomised to each arm). This will provide 80% power at a 5% one-sided significance level to detect an absolute reduction of 20 percentage points in 9-month PFS. This number of patients would also be sufficient to demonstrate non-inferiority of the extended frequency arm, using a hazard ratio non-inferiority margin of 1.94 for the renal cohort (and e.g. 1.85 for the melanoma cohort) which should correspond to a 20-percentage points NI margin on the 9-month PFS difference scale. 9-month PFS rates are estimated to be 70% in the renal cohort [1,18]. For all cohorts, stage I analysis will be performed when approximately 30 PFS events have been observed in the control arm, which is expected to occur around six months after the completion of recruitment.

Following analysis of stage I data, assuming satisfactory outcomes in patients treated with the extended dosing interval, stage II will then test multiple experimental arms with the maximal interval being 3 times the SOC. The second stage intends to enrol up to an additional 200 patients per cohort dependent on stage I results. Under the same assumptions made for the stage 1 sample size calculations, this will provide around 80% power to demonstrate non-inferiority for the extended interval arm, relative to SOC using the same non-inferiority margins.

### Health economic considerations

2.4

The economic evaluation for stage I of the trial will evaluate the relative cost-effectiveness of the two treatment frequencies over a 12-month period. The incremental cost per quality-adjusted life-year (QALY) gained will be calculated as recommended by the National Institute for Health and Care Excellence (NICE) [19], using QALYs calculated from EQ-5D-5L responses collected at baseline and every 12 weeks, including after progression [20], from the perspective of the NHS and Personal Social Services.

Resource use will be collected at baseline for the preceding 12 weeks and every 12 weeks thereafter from patient records and directly from participants via a modified version of the Client Service Receipt Inventory (CSRI) [21], covering inpatient and outpatient hospital service use, urgent care, primary and community health and social care service contacts, and therapies including ICI treatment costs, radiotherapy, surgery, and other systemic cancer treatments. Costs involved in administering ICI will be included in both arms.

Parameter uncertainty will be addressed using standard boot-strapping techniques and sensitivity analyses performed for any assumptions made. Further details will be described in the statistical and health economic analysis plan.

A lifetime decision analytic model will be constructed using information collected in stage I and stage II for those arms that are carried forward, to estimate the relative cost-effectiveness of the different treatment frequencies.

